**Fig. 2 Fig2:**
[figure not shown]
Graphic representation of the sample size definition

### Recruitment {15}

A physician will recruit patients via an active search. She/he will perform visits three times a day (9 am, 3 pm, 9 pm) to the sites of the hospital that will receive patients with suspected COVID-19, such as the emergency room, COVID-19-dedicated wards, and ICUs. She/he will also determine whether the patient meets the eligibility criteria for the study, expedite the exams required to comply with the inclusion criteria (RT-PCR for SARS-CoV-2 and computed tomography of the chest), and will make immediate contact with the study coordinator for enrollment.

## Assignment of interventions: allocation

### Sequence generation {16a}

We will use a software-based approach (www.sealedenvelope.com) to generate the allocation sequence using a blocked randomization with randomly selected block sizes, with 3, 6, or 9 subjects per block. To reduce the probability of imbalance between the groups with regard to severity, we have set up a stratification approach using two strata: (1) no oxygen support needed or oxygen support < 3 L/min delivered by nasal catheter; (2) high-flow oxygen support delivered by nasal catheter between 3 L and 6 L/min or up to 10 L/min by non-rebreather face mask, 35% oxygen through a Venturi mask, non-invasive ventilation, or mechanical ventilation or eventually ECMO.

### Concealment mechanism {16b}

Sealed and sequentially numbered opaque envelopes, containing the allocation arm, will be prepared in advance according to the randomization list. These envelopes will be stored in one of the ICUs dedicated to COVID-19 at the Clinics Hospital of the University of Campinas. Once the eligibility criteria have been met and the form has been signed, the study coordinator (using a central telephone or message) will double-check with the assistant physician the exact envelope number corresponding to the patient’s allocation following an established standard procedure. The same physician should then open the envelope and soon after prescribe the therapy according to the arm specified in the envelope.

### Implementation {16c}

The randomization list will be generated by an independent researcher, who will not have any other involvement in the study. The project coordinator and investigators in each unit of the hospital (wards, emergency department, and ICUs) will enroll the participants after contacting (central telephone, message, in-person) the physician responsible for the active search in the hospital reporting eligible patients. An attending physician will allocate the patient by opening the sequential envelope in virtual contact with the central telephone and assign participants to interventions.

## Assignment of interventions: blinding

### Who will be blinded {17a}

This is an open-label trial because neither the trial participant nor the care providers will be blinded. However, the data entry staff and data manager will be blinded. The data will be sent to the data entry staff by code, and the study arm will not be specified. The data entry staff and data managers are not part of the hospital staff and will not have access to any clinical data belonging to the patients. The Data Safety Monitoring Board (DSMC) will be unblinded.

### Procedure for unblinding if needed {17b}

This does not apply because it is an open-label study. We consider that there will be no need to unblind data entry staff or data managers, as they are not involved in the course of patient care.

## Data collection and management

### Plans for assessment and collection of outcomes {18a}

Baseline data, other trial data, and outcome data will be collected by all investigators participating in this study and will be stored in the Research Electronic Data Capture (REDCap) platform. The investigators will be trained to apply the seven-category ordinal scale in order to collect the outcome data. Data will be collected daily by one investigator on site using a datasheet available online and in print form.

### Plans to promote participant retention and complete follow-up {18b}

Volunteers can withdraw their consent during any stage of the study, without prejudice to their individualized treatment. In this situation, the investigator will clarify any doubts and inform them of the potential benefits of being in the study. The patient’s withdrawal will be reported in the eCRF, and the outcome will be assessed on the day of withdrawal and the patient will be invited to return if possible for an additional visit after the study has closed, in order to collect data on adverse events. Patients excluded due to adverse events will be followed up to day 28, or until necessary. Patients with any deviation in the intervention, due to risk or request, will have their outcomes collected normally according to the proposed timeline.

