### Criteria for discontinuing or modifying allocated interventions {11b}

Withdrawal of consent. This item follows the Declaration of Helsinki, in which the patient has the right to withdraw his consent without any prejudice regarding the treatment offered to him/her by the clinical provider.Grade 4 adverse reaction (life-threatening consequences) as stated by Common Terminology Criteria for Adverse Events (CTCAE) v6.0 used for oncology drugs by the National Cancer Institute (NCI).Protocol violation.Allergic reactions to any drug or any other situation deemed to jeopardize patient safety.

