### Data management {19}

Each subject allocated in the study will be given a unique code generated by the statistician responsible for the randomization list (all possible identifiers will be removed). This code will be maintained by the PI and the lead coordinator in a password-protected file, which will not be accessible to the data management team or other investigators. All data included (outcome, questionnaires, clinical data, computed tomography, biochemical analysis) will be retrieved from the online official medical record of the hospital and will be uploaded into REDCap. Data will be collected daily by one investigator on site using a datasheet available online and in print form. Collected data will be sent by email to two researchers in the data management team in order to establish double data entry, as well as to an independent company reviewing the quality of the data, and the data management team, which is responsible for range checks for data values. A Standardized Operational Protocol for data collection will be available as supplementary material.

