## Statistical methods

### Statistical methods for primary and secondary outcomes {20a}

All our statistical analyses will follow the intention-to-treat principle. For the primary outcome, we will use the Kaplan-Meier estimator and log-rank test to respectively estimate and compare the survival curves, followed by a Cox proportional hazards model to adjust for baseline explanatory variables in the final data analysis. Multiple imputation will be used to impute missing data. The following covariates will be settled: age, sex, duration of symptoms before enrollment, use of oxygen support prior to enrollment, and presence of relevant comorbidities. This analysis will be performed to compare each treatment arm, that is, the icatibant plus standard care group and the C1 esterase group inhibitor plus standard care, with the standard care group alone. In the analysis of secondary endpoints involving time to event, such as duration of mechanical ventilation (days) and length of hospitalization in survivors (days), we will also use the Cox proportional hazards model. The logistic regression model will be used to analyze secondary binary endpoints.

The statistical analysis plan (SAP) containing all the details of the analysis will be finalized and made available to the DSMC before the final analysis.

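### On withdrawal of consent, primary-outcome assessment stops that day without asking whether the hospital record may be read to day 28

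*Protocol article*

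**What the plan says.** Section {18b} (retention and follow-up) of the protocol article sets three rules.

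- **Consent withdrawn.** The trigger is "Volunteers can withdraw their consent during any stage of the study, without prejudice to their individualized treatment". Then "the outcome will be assessed on the day of withdrawal and the patient will be invited to return if possible for an additional visit", which takes place "after the study has closed, in order to collect data on adverse events".
- **Excluded because of an adverse event.** The patient is followed to day 28, or longer if needed.
- **Deviation from the allocated treatment.** "Patients with any deviation in the intervention, due to risk or request, will have their outcomes collected normally according to the proposed timeline".

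Section {11b} (criteria for discontinuing or modifying interventions) begins its list with "Withdrawal of consent. This item follows the Declaration of Helsinki" and adds that "the patient has the right to withdraw his consent without any prejudice regarding the treatment offered to him/her by the clinical provider". It does not say whether a patient who stops the drug also leaves data collection.

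Three other sections bear on this. Section {11c} expects the patient to be in hospital throughout follow-up. Section {19} says that the outcome and clinical data "will be retrieved from the online official medical record of the hospital". Section {20a} says "All our statistical analyses will follow the intention-to-treat principle".

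**The concern.** The primary outcome is the time from randomization to a two-point improvement on the seven-category scale or live discharge; the sample-size section takes it as censored at day 28. A patient who withdraws consent on, say, day 3 has one last assessment that day. The only later contact is for adverse events, so the plan provides no route to the improvement date, discharge date or vital status.

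The trial is open-label, and repeated injections or infusions exist only in the two drug arms. Withdrawal could therefore differ by arm and be related to how the patient is doing. If so, censoring at withdrawal is informative and the intention-to-treat comparison is distorted. Multiple imputation, as planned in {20a} and {21c}, would not reliably repair this if withdrawal depends on prognosis that was not recorded.

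Much of this loss may be avoidable. Live discharge is itself an event, so a living patient who has not yet had the event would ordinarily still be in this hospital, with the outcome in its record. What is missing is a step asking for permission to read it.

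**Working it through.** **1. Which rule applies to whom**

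| Situation | Rule in {18b} | Outcome to day 28? |
|---|---|---|
| Patient asks only to stop the drug | Deviation by request | Yes, on the normal timeline |
| Patient is excluded for an adverse event | Follow-up to day 28 | Yes |
| Patient withdraws consent | Assessed that day; adverse-event visit after closure | No, by implication |

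The triggers differ, so the rules do not collide. The weak spot is the line between rows 1 and 3. Section {11b} lists consent withdrawal as a reason to stop the intervention and gives no test for telling it from a request to stop the drug. Two investigators could code the same refusal differently, and one coding would end outcome collection.

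**2. The plan's sample size, for scale**

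Inputs from {14}: hazard ratio 1.9, alpha 2.5% (taken as two-sided, which reproduces the stated size), power 80%, drop-out (censoring) 20%, factor 1.5 for the third arm.

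- Events per comparison: 4 × (2.241 + 0.842)² / (ln 1.9)² = 92.3.
- Patients per comparison: 92.3 / 0.80 = 115.4, rounded up to 116.
- Total: 116 × 1.5 = 174, or 58 per group. This matches the plan.

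If withdrawals fall within the 20% allowance, planned power does not change. If they come on top of it, power at a hazard ratio of 1.9 with 116 patients goes from 80.2% (no extra loss) to 79.4% (2%), 78.0% (5%), 75.5% (10%) and 70.0% (20%).

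**3. Possible bias in the hazard ratio**

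The protocol gives no withdrawal rate and no control improvement rate, so these are assumptions: no true effect, exponential times, 75% improving by day 28 in both arms. A fraction f of one drug arm, all of whom would not have improved by day 28, is censored on day 3.

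- Daily rate: −ln(0.25)/28 = 0.0495.
- Mean time at risk per patient to day 28: 0.75/0.0495 = 15.15 days.
- Each lost non-improver gives up 28 − 3 = 25 days at risk and no event, so the rate ratio is about 15.15 / (15.15 − 25f).

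| Lost from one drug arm | Patients of 58 | Rate ratio by formula | Simulated Cox hazard ratio |
|---|---|---|---|
| 2% | about 1 | 15.15/14.65 = 1.03 | 1.03 |
| 5% | about 3 | 15.15/13.90 = 1.09 | 1.09 to 1.10 |
| 10% | about 6 | 15.15/12.65 = 1.20 | 1.20 to 1.21 |

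Sensitivity of the simulated hazard ratio:

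- 60% to 80% improving: about 1.07 to 1.10 at 5% lost, and 1.16 to 1.24 at 10%.
- Censoring on day 7 (75% improving): 1.08 at 5% and 1.17 at 10%.
- Withdrawal unrelated to prognosis, 10% lost: 1.00.
- Equal selective loss in both arms: 1.00.
- Selective loss in the control arm only: the reciprocals, about 0.97, 0.92 and 0.83.

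**The case against.** A reader might infer that {18b} gives opposite instructions for a patient who refuses further doses. It does not. That patient has made a deviation by request, and the last sentence of the section gives one answer: outcomes are collected as usual. That {11b} lists consent withdrawal among the reasons for discontinuation does not turn every drug stop into a withdrawal of consent. So the stops most likely to be informative, refusal and intolerance, are already followed. This objection stands in full; only the risk of misclassification remains.

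Ending collection when consent is withdrawn is also a conventional rule and can be ethically required. The existence of a record does not authorise anyone to read it. This stands too, and for that reason the remedy is to ask, and to stop if the patient refuses.

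It can further be said that the consent form or an operating procedure may already hold such a step, since the article is condensed and consent pages are not shown. That is possible. But {18b} does state a rule, and as written it makes the day of withdrawal the last outcome assessment and limits the later visit to adverse events.

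Finally, the hazard ratios above 1.00 are a one-sided worst case: every lost patient is a non-improver, all are in one arm, and none is lost from the other. This is correct. The 20% allowance cannot be used to make them likely either, because it is labelled as censoring and is not a forecast of consent withdrawals.

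**Conclusion.** The point holds in a limited form. For patients who withdraw consent, the stated rule ends primary-outcome assessment that day by implication (the text does not say so outright). It does so without seeking permission for record-based follow-up that the plan's own setting makes easy. Daily data collected before withdrawal are kept, so the loss concerns only the period from withdrawal to day 28. The boundary with a simple request to stop the drug is not drawn in {11b}, so some patients who should be followed could be coded as withdrawals.

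The size is unknown. Under the assumptions shown, the distortion runs from none (hazard ratio 1.00) to about 1.20 with a selective 10% loss from one drug arm, and in the opposite direction if the loss is in the control arm. Two stronger conclusions are not supported: that the section contradicts itself, and that a bias of this size should be expected. The sample size is unaffected unless losses exceed the 20% allowance. This is a cheap improvement worth making, not a flaw that invalidates the design.

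**What to change.** 1. In {11b} and {18b}, state that a request to stop the study drug is not a withdrawal of consent for data, and that such patients stay on the normal outcome timeline.
2. In {18b}, when consent is withdrawn, ask whether the hospital record may still be read to day 28 for ordinal category, discharge date and vital status. Stop collection only if the patient refuses.
3. Add one eCRF field for the type of withdrawal: drug only, visits and procedures but record access allowed, or all data use refused. Report the counts by arm.

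The cost is an amendment to the protocol and consent wording, with ethics committee approval as {25} requires, one eCRF field, and some extra record reading for each patient who agrees. No additional patients or procedures are needed, and no treatment rule changes.

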### Data management {19}

Each subject allocated in the study will be given a unique code generated by the statistician responsible for the randomization list (all possible identifiers will be removed). This code will be maintained by the PI and the lead coordinator in a password-protected file, which will not be accessible to the data management team or other investigators. All data included (outcome, questionnaires, clinical data, computed tomography, biochemical analysis) will be retrieved from the online official medical record of the hospital and will be uploaded into REDCap. Data will be collected daily by one investigator on site using a datasheet available online and in print form. Collected data will be sent by email to two researchers in the data management team in order to establish double data entry, as well as to an independent company reviewing the quality of the data, and the data management team, which is responsible for range checks for data values. A Standardized Operational Protocol for data collection will be available as supplementary material.

### Confidentiality {27}

The personal information of the allocated patient and the enrolled patient collected by the investigator will be identified by the same individualized code generated for the randomization list. The data will be entered into the CRF using this code. The identification of this code will not be known by the researchers and will be kept in a password-protected document in a spreadsheet maintained in a cloud accessible by the PI and the coordinator.

### Plans for collection, laboratory evaluation, and storage of biological specimens for genetic or molecular analysis in this trial/future use {33}

The nasopharyngeal/oropharyngeal swabs for RT-PCR will be collected by the patient care provider team and sent to the hospital’s laboratory in accordance with the local protocol, as well as for routine exams. RNA from whole blood, serum, and plasma samples will be stored for future use in ancillary studies, which will need approval from local ethics committees.

## Statistical methods

### Statistical methods for primary and secondary outcomes {20a}

All our statistical analyses will follow the intention-to-treat principle. For the primary outcome, we will use the Kaplan-Meier estimator and log-rank test to respectively estimate and compare the survival curves, followed by a Cox proportional hazards model to adjust for baseline explanatory variables in the final data analysis. Multiple imputation will be used to impute missing data. The following covariates will be settled: age, sex, duration of symptoms before enrollment, use of oxygen support prior to enrollment, and presence of relevant comorbidities. This analysis will be performed to compare each treatment arm, that is, the icatibant plus standard care group and the C1 esterase group inhibitor plus standard care, with the standard care group alone. In the analysis of secondary endpoints involving time to event, such as duration of mechanical ventilation (days) and length of hospitalization in survivors (days), we will also use the Cox proportional hazards model. The logistic regression model will be used to analyze secondary binary endpoints.

The statistical analysis plan (SAP) containing all the details of the analysis will be finalized and made available to the DSMC before the final analysis.

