### Sample size {14}

We used information from the previously published LOTUS [3] trial evaluating the effect of lopinavir-ritonavir on time to clinical improvement (TTCI) [censored at day 28], since there is no information on the effect of icatibant or C1 esterase inhibitor for this primary outcome. This approach resulted in a hazard ratio of 1.24 for clinical improvement. It is also relevant to take into account the emergency situation and the high costs involved. The sample size was determined based on the formula for the proportional hazard regression model (Schoenfeld, 1983). We assumed a 5% type 1 error (alpha), power test of 80%, drop-out (censure) rate of 20%, and hazard ratio between treatment and the standard care alone varying from 1.2 to 2.0. To extend the calculations for a three-arm trial, we considered the three groups of the same size and the comparison of the two treatments separately to standard care alone, but without comparing the two treatments to each other. In other words, the same standard care alone group will be compared with each treatment group. Additionally, we set alpha at 2.5% to allow for multiple testing and multiplied the sample size by 1.5. Figure 2 presents the total sample size required for this setup and according to different hazard ratios. Assuming a hazard ratio of 1.9, we obtained a final sample size of 174 (58 per group).

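### Randomisation is stratified by oxygen support, but the primary log-rank test names no strata and the Cox covariate list does not contain the randomisation stratum; aligning them may protect power at no cost in patients

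*Protocol article*

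**What the plan says.** Under Sequence generation {16a}, the protocol article states "we have set up a stratification approach using two strata", with the aim of limiting imbalance in severity. Stratum 1 is "no oxygen support needed or oxygen support < 3 L/min delivered by nasal catheter". Stratum 2 begins with "high-flow oxygen support delivered by nasal catheter between 3 L and 6 L/min or up to 10 L/min by non-rebreather face mask" and runs up to mechanical ventilation and ECMO. The cut therefore falls among patients who are already on oxygen.

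Under Statistical methods for primary and secondary outcomes {20a}, the primary comparison is given as "we will use the Kaplan-Meier estimator and log-rank test to respectively estimate and compare the survival curves". An adjusted analysis is planned as the next step: "followed by a Cox proportional hazards model to adjust for baseline explanatory variables in the final data analysis". The covariates are "age, sex, duration of symptoms before enrollment, use of oxygen support prior to enrollment, and presence of relevant comorbidities". Neither analysis mentions the randomisation stratum. Details are deferred to a SAP that is not shown.

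The section on interim analyses uses a Cox model for the primary outcome, without saying how it is adjusted. The section on subgroup analyses splits severity into room air or catheter oxygen on one side, and high-flow oxygen, non-invasive or invasive ventilation or ECMO on the other. It gives no flow threshold.

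**The concern.** A factor that is thought important enough to stratify on normally enters the primary analysis. Leaving out a prognostic stratification factor has two effects in a time-to-event comparison. The unstratified log-rank test becomes conservative, because stratified allocation has removed between-arm variation that the test's variance still counts. The unadjusted hazard ratio also moves toward 1 relative to the within-stratum value.

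The stratum is plausibly prognostic here. The middle categories of the seven-category outcome scale are levels of respiratory support, and the stratum is a cut of the same quantity at baseline. With only about 93 events per comparison there is little power to spare.

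The oxygen covariate in the Cox model does not clearly fill the gap. Read as yes or no, it would put a patient on 1 L/min by catheter together with a ventilated patient, whom the randomisation separates.

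**Working it through.** **1. The plan's own figure.** Inputs from Sample size {14}: hazard ratio 1.9, 80% power, 20% drop-out or censoring, and "we set alpha at 2.5% to allow for multiple testing and multiplied the sample size by 1.5". Sidedness is not stated; a two-sided 2.5% reproduces the stated total.

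- Events (Schoenfeld): (2.2414 + 0.8416)² / (0.25 × (ln 1.9)²) = 9.505 / 0.1030 = 92.3.
- Two arms: 92.3 / 0.8 = 115.4. Three arms: 115.4 × 1.5 = 173.0, so 58 per group and 174 in total, as stated.
- Power check: 116 × 0.8 = 92.8 events; √(92.8 × 0.25) × 0.6419 − 2.2414 = 0.850, which gives 80.2%.

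The formula has no stratum term, so it does not say whether 1.9 is a within-stratum or a marginal hazard ratio.

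**2. Log-rank test with and without strata.** This was simulated with 58 per arm, allocation balanced within strata, exponential times, censoring at day 28, 80% events overall and two-sided 2.5%, in 3,000 runs per scenario. Assumed, because the protocol does not give them: a within-stratum treatment hazard ratio of 1.9, 30% or 50% of patients in stratum 2, and the hazard ratio for improvement of stratum 2 versus stratum 1. Each cell shows 30% / 50% in stratum 2.

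| Assumed stratum HR | Power, unstratified | Power, stratified | Null rejection, unstratified |
|---|---|---|---|
| 1.0 | 79.7 / 80.0% | 79.2 / 79.5% | 2.7 / 2.7% |
| 0.7 | 79.7 / 79.2% | 79.7 / 80.1% | 1.8 / 2.3% |
| 0.5 | 74.9 / 74.1% | 79.8 / 79.2% | 2.3 / 1.7% |
| 0.35 | 70.3 / 66.4% | 80.5 / 79.3% | 1.3 / 1.4% |
| 0.25 | 57.5 / 54.8% | 77.8 / 78.6% | 0.7 / 1.0% |

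The Monte Carlo standard error of a power near 80% is √(0.8 × 0.2 / 3000) = 0.7 points. Loss from not stratifying: 0-1 point at 0.7, about 5 at 0.5, 10-13 at 0.35, and 20-24 at 0.25.

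**3. Cox model.** Same set-up, 2,000 runs, with an assumed mix of 15% on no oxygen, 45% below 3 L/min and 40% in stratum 2. Entries are unadjusted / adjusted for any oxygen (yes or no) / adjusted for stratum.

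| Assumed hazards (none, <3 L/min, stratum 2) | Power | Estimated HR |
|---|---|---|
| 1, 1, 0.7 | 78 / 78 / 80% | 1.88 / 1.90 / 1.92 |
| 1, 1, 0.5 | 75 / 75 / 81% | 1.83 / 1.85 / 1.93 |
| 1, 1, 0.35 | 66 / 68 / 79% | 1.74 / 1.76 / 1.92 |
| 1, 0.7, 0.35 | 70 / 73 / 78% | 1.79 / 1.84 / 1.90 |

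With no prognostic effect all three models give 1.92-1.93, so attenuation should be judged against about 1.92. A yes/no covariate recovers little.

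**4. If the oxygen covariate is coded by level.** Here 1,500 runs used an assumed mix of 15/45/25/15% over no oxygen, <3 L/min, 3-10 L/min and higher support. With level hazards 1/1/0.5/0.5, Cox power was 76% unadjusted, 76% with yes/no, 81% with stratum and 80% with level. With 1/0.8/0.5/0.25 it was 71%, 72%, 78% and 79%. A level-coded covariate would recover the loss in the Cox model, but not in the log-rank test.

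**5. The definitions side by side.** A patient on 4 L/min by nasal catheter is in stratum 2 at randomisation. In the Cox list the same patient is an oxygen user, with categories not given. In the subgroup section this patient is less severe if catheter oxygen decides, but more severe if high flow is read as the randomisation section uses the term. The three sections do not share one severity variable.

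**The case against.** The strongest counter-argument is that the article condenses a longer plan and leaves the details to a SAP. Stratifying the log-rank test and coding a covariate are details that a SAP often supplies, and the text never says that the test will be unstratified. This lowers the weight of the point but does not remove it. The protocol positively names the test and lists the covariates, and that list omits the stratum.

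A reader might infer that the planned power is lost. The documents do not support that. No prognostic effect is given, and the 174 comes from a formula without strata. If 1.9 is read as a marginal hazard ratio, the plain log-rank test keeps about 80%. Losses above 20 points need an extreme stratum hazard ratio of 0.25. The endpoint is also improvement from the patient's own starting category. In categories 3 and 4 the event in effect means live discharge, whereas in 5 and 6 it can occur in hospital. A large gap between strata therefore cannot be presumed.

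A reader might also infer that the oxygen covariate is a yes/no variable and should be replaced by the stratum. The coding is not stated. If it carries levels, it holds information that the stratum lacks, because stratum 2 pools 3 L/min by catheter with ventilation and ECMO. The stratum should be added, not substituted.

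Finally, the error runs in the safe direction: null rejection was 0.7-2.7% against a nominal 2.5%.

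**Conclusion.** The mismatch is real. The strata used for randomisation appear neither in the log-rank test as stated nor in the Cox covariate list, and the severity subgroup is split differently again. If the strata are prognostic, the unstratified test is conservative and the hazard ratio is attenuated. This does not threaten validity.

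The size rests on assumptions: a within-stratum hazard ratio of 1.9, 30-50% of patients in stratum 2 and 80% events. Across the log-rank and Cox simulations the loss is then about 0-2 points of power at a stratum hazard ratio of 0.7, about 5 at 0.5 and 10-14 at 0.35. The estimate falls from about 1.92 to 1.83 at 0.5 and to 1.74 at 0.35. Age, symptom duration and comorbidities were not simulated, and the SAP may already specify a stratified test. This is a free improvement, not a flaw that undermines the trial.

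**What to change.** - In {20a}, name a log-rank test stratified by the two randomisation strata as the confirmatory test for each of the two comparisons with standard care.
- In {20a}, stratify the Cox model by the randomisation stratum, or add it as a covariate. Keep the listed covariates, including oxygen support, and state the categories of the latter.
- In the interim analysis section, use the same stratified Cox model.
- Reconcile the severity definitions in the randomisation, analysis and subgroup sections, or say that they differ on purpose and why.

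The cost is a few sentences, made before outcome data are compared by arm. The protocol's section on amendments requires changes to the statistical analysis to go to the ethics committee. No patients and no new data are needed, because the stratum is known for everyone randomised, and the sample size stays at 174.
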